### Statistical analyses

For the primary analyses the main endpoint is change in mean number of hours/24 h spent with excessive crying before and after the two weeks treatment period, comparing treated and not treated children (mean difference in hours of crying with standard deviations and *p*-value for difference between the groups using a two-sample t-test). Change in mean hours before and after equals 3–4 days before treatment and 3–4 days after treatment. All analyses will be performed by intention-to-treat principles and no data will be imputed.

To evaluate the independent effect of treatment, multiple linear regression analyses of the change in crying hours will be performed including baseline values of the crying hours, randomization group and stratification factors as independent variables.

Secondary outcomes will be analyzed similarly. Furthermore, a secondary repeated measures linear regression analysis will evaluate change over time with regard to time spent crying, sleeping, and time being awake and content.

In a secondary explorative analysis it will be evaluated if subgroups of children with suspected musculoskeletal problems will benefit more from the intervention than others, and all analyses will be repeated stratified for presence of musculoskeletal problems. This hypothesis is based on the theory that the children cry because of pain that origins from the musculoskeletal system [27]. Furthermore, existing literature suggest there may be a relationship between complicated births and infantile colic [20, 34], and one theory is that complicated births may induce musculoskeletal problems [23, 27]. We therefore hypothesized that a potential beneficial treatment effect of chiropractic care may be greater for the children born by a complicated birth when compared to the children born at an uncomplicated birth. Therefore, similarly to presence of musculoskeletal problems, analyses will be repeated stratified for elected factors related to birth. These analyses will be explorative in nature, but could help to identify potential clinical predictors of treatment effects to be incorporated in future studies. Analyses will also be performed on the different age and chiropractor strata.

In the stratified secondary analyses, clinical relevant confounders will be included in the analyses in consideration of the number of individuals in each stratum. These analyses will only be performed when there are a sufficient number of individuals in the strata.

All results will be published in relevant peer reviewed scientific journals and subsequently in the Danish media.

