### Randomization and blinding

The allocation occurs through a 1:1 ratio by a predetermined restricted randomization scheme. The participants are stratified according to their age at enrollment (2–6 weeks; 7–10 weeks; 11–14 weeks) and the treating chiropractor. The eligible participants are randomly assigned in blocks of 4 to 6, according to computer-generated random numbers, to be enrolled in either the intervention or control group.

The computer generated block randomization was administered by a research assistant, not otherwise involved in the outcome measurements or the intervention. The research assistant then wrote the consecutive letters A and B on separate pieces of paper and then placed them in sealed opaque envelopes, which were given to each chiropractor. To take the above mentioned stratification into account the procedure was repeated and a different list of group allocation was made for each age level and each chiropractor in the study. When a child is randomized and an appointment booked, the PI informs the clinic of the next randomization number for that specific chiropractor and age group (which is a coded number not revealing group allocation). Only the chiropractor has the list that reveals if that certain randomization number means allocation to intervention or control group.

Hence, the intervention in this trial makes blinding of care providers impossible. The parents are blinded to their child’s allocation group during the project period. To uphold blinding of the randomization, all parents leave the chiropractor’s consultation room for a few minutes after history taking and examination, while the treatment is (or is not) carried out. For the analyses, the coding of intervention and control groups will be concealed from the PI and the statisticians performing the analyses. The randomization code will not be broken until the analyses are completed.

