#### Potential clinical predictors

Musculoskeletal problems as based on information from interview-based questionnaires and the chiropractors’ examination defined by favorite side during feeding or sleep, does not want to lie in abdominal position, difficulties dressing/undressing the child, objective signs as asymmetric gluteal folds/hips/knees/tonus in back musculature or skew position/C-curve and dichotomized into yes/noFactors related to pregnancy or birth e.g. complications related to pregnancy, induction of labor, duration of birth and different stages in birth, abnormal presentation in birth canal, interventions in birth such as vacuum assisted delivery and cesarean. This information will be drawn from interview-based questionnaires and supplemented if needed from hospital records and dichotomized into yes/no or categorized into appropriate categories.

Potential confounders include parental highest attained education, cohabitation status, smoking status of parents, birthweight, siblings with history of colic, stress in everyday life, severe stress related episodes during pregnancy or birth (e.g. severe illness or death among family members or close friends), mental illness of mother (e.g. depression). This information is obtained from the interview-based questionnaires. Other potential confounders are age and treating chiropractor which is accounted for in the stratified block randomization.

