### Sample size

Based on data from the pilot study we observed a mean reduction in hours of crying in the control group of 2.5 h per day before and after treatment with a standard deviation of 2.5 h. Based on group discussions in the research group to obtain a clinically satisfactory result, we therefore wish that children in the intervention group will have a reduction of one additional hour, resulting in a reduction of 3.5 crying hours. With an assumption of a common standard deviation of 2.5, a level of significance on 0.05 and a power of 80%, this result in a sample size of 200 children distributed with 100 in each group.

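### The primary test is an unadjusted t-test on change, although a baseline- and strata-adjusted regression of the same change is already planned: valid, but precision is given away

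*Protocol article*

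**What the plan says.** All references are to the protocol article, which is the only document available.

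- **Primary analysis (Statistical analyses).** The article says "the main endpoint is change in mean number of hours/24 h spent with excessive crying before and after the two weeks treatment period". Treated and untreated children are compared by mean difference, with a p-value "for difference between the groups using a two-sample t-test". No covariate is mentioned.
- **Adjusted analysis (same section, next paragraph).** To assess the independent effect of treatment, the same change is to be regressed in a model "including baseline values of the crying hours, randomization group and stratification factors as independent variables". This model is given no rank relative to the t-test.
- **Design (Randomization and blinding).** Allocation is 1:1, in blocks, stratified by three age bands and by treating chiropractor. Visit 2 gives seven chiropractors in four clinics. The pilot results section says the stratification was added because these factors may influence outcome.
- **Confounders (Potential clinical predictors).** "Other potential confounders are age and treating chiropractor which is accounted for in the stratified block randomization".
- **Sample size.** The calculation assumes that "children in the intervention group will have a reduction of one additional hour, resulting in a reduction of 3.5 crying hours". The other inputs are "With an assumption of a common standard deviation of 2.5" and "a level of significance on 0.05 and a power of 80"%, which lead to 100 children per group.

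**The concern.** The design spends effort on two sources of precision that the primary test does not use.

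- **Baseline crying.** A change score subtracts the whole baseline, which fixes the slope of follow-up on baseline at 1. Children enter because they cry a lot, so some regression to the mean is likely and the true slope is then likely to be below 1. A regression estimates the slope and removes the excess noise.
- **Strata.** Stratified randomization balances age and chiropractor between arms. The t-test's standard error still includes the variation between strata, so the gain from balancing never reaches the p-value.

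At stake is the power of the primary comparison. It is planned at 80% with no stated allowance for missing diaries and no imputation, while a model that is usually sharper stands in the next paragraph of the plan.

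**Working it through.** **Inputs from the document.** Difference 1 h (3.5 against 2.5), SD of change 2.5 h, alpha 0.05, power 80%, 100 per arm. Sidedness is not stated. I take it as two-sided, which reproduces the stated size.

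**1. The plan's own figure.** The normal approximation gives n per arm = 2 × (1.960 + 0.842)² × 2.5² / 1² = 98.1, so 99. The noncentral t gives 99.08, so 100, as stated. Power of the t-test at 100 per arm is 80.4%.

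**2. Variance ratio, adjusted to unadjusted.** Let k = follow-up SD / baseline SD and r = the before-after correlation. In units of the baseline variance:

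- variance of change = 1 + k² − 2rk
- residual variance after adjusting for baseline = k²(1 − r²)
- first minus second = (1 − rk)², which is never negative and is zero only when rk = 1

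In large samples the adjusted analysis is therefore never less precise. The ratio is k²(1 − r²) / (1 + k² − 2rk), which reduces to (1 + r)/2 when k = 1. Regressing change on baseline gives the same treatment estimate as regressing follow-up on baseline, so this applies to the model as planned.

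**3. Charge for the extra terms.** Baseline (1), age band (2) and chiropractor (6) reduce the residual degrees of freedom from 198 to 189. I charge a variance factor of 198/189 = 1.048. This is on the pessimistic side, because the strata are roughly balanced by design and I credit them with explaining nothing.

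**4. Power at 100 per arm**, 1 h difference, SD of change held at 2.5 h. Residual SD = 2.5 × √ratio. Both k and r are assumptions.

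| k | r | ratio | residual SD (h) | power | power after charge |
|---|---|---|---|---|---|
| 1 | 0.3 | 0.65 | 2.02 | 94% | 93% |
| 1 | 0.5 | 0.75 | 2.17 | 90% | 89% |
| 1 | 0.7 | 0.85 | 2.30 | 86% | 85% |
| 1 | 0.9 | 0.95 | 2.44 | 82% | 81% |
| 1.25 | 0.7 | 0.98 | 2.48 | 81% | 79% |
| 1.5 | 0.5 | 0.96 | 2.45 | 82% | 80% |
| 1.5 | 0.7 | 1.00 | 2.50 | 80% | 79% |
| 0.8 | 0.5 | 0.57 | 1.89 | 96% | 95% |
| 0.67 | 0.5 | 0.43 | 1.64 | 99% | 99% |

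The worst case is a ratio of 1 with the full charge: 78.5% against 80.4%, a loss of about two points.

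**5. Ignoring the strata.** If strata explain a share R² of the outcome variance, the t-test's true two-sided size is about 2 × [1 − Φ(1.96 / √(1 − R²))]. Assuming R² = 0.05 gives 0.044, and R² = 0.10 gives 0.039. Both are below 0.05, so the test is conservative.

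**The case against.** The case for leaving the plan alone is respectable.

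- **Design and test agree.** A t-test on change is valid in a randomized trial, and the sample size was built for exactly this test. A reader might infer that the analysis is biased, underpowered or inflates type I error. The document supports none of these. Missing a true 1 h effect one time in five is the risk the plan openly accepts. This stands.
- **The statement on age and chiropractor is not wrong.** A reader might take it as a false claim that stratifying replaces adjustment. It concerns confounding, and stratified randomization does address that. Only the standard error needs the factors in the model. This stands.
- **The size of the gain is unknown.** Inclusion requires at least three hours of crying a day, which could narrow the baseline spread and push k above 1. Quoting only the equal-SD gains would overstate what can be shown. This stands, and is why the table covers both directions.
- **Choosing between two results.** A reader might infer that two analyses of one endpoint invite selection after the fact. The t-test is placed under the primary analyses, and group coding is concealed from the investigator and statisticians until the analyses are complete. Choice by significance is not ruled out, but the worry is weak.
- **The regression is already in the plan.** The sentence that secondary outcomes are handled similarly follows both analyses, so the two could be read as a pair. No estimate would be lost as things stand. This means the dispute is only about rank, but rank decides which p-value counts.

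**Conclusion.** The point holds as a matter of efficiency. The primary test leaves out baseline crying and the stratification factors, which the trial collects and already plans to model. The direction is well supported: in large samples adjustment for baseline cannot lose precision, and ignoring the strata makes the t-test slightly conservative.

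The size is not settled by the document. It rests on r and k, neither of which is given, and on a two-sided alpha. For k from 0.67 to 1.5 and r from 0.2 to 0.7, power after the covariate charge runs from about 79% to above 98%, against 80.4% for the t-test. The possible loss is about two points, while under equal SDs and r of 0.3 to 0.7 the net gain is about 4 to 12 points. This is a worthwhile improvement to a sound analysis, not the repair of an invalid one.

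**What to change.** Before the randomization code is broken, name the regression already described (baseline crying hours, arm, age stratum, treating chiropractor) as the single primary analysis. Report its adjusted mean difference with a 95% confidence interval. Keep the two-sample t-test as a supportive, unadjusted summary.

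No new data are needed and the sample size of 200 need not change. Any precision gained would offset some loss from missing diaries. The cost is a protocol amendment, which the ethics committee reviews according to the Ethics section, and nine residual degrees of freedom. According to Trial status, recruitment was still ongoing when the article was written.

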**Discussion:**

In a single-blind randomized controlled design we will evaluate the effectiveness of chiropractic treatment on infantile colic. The study will contribute to determine the effect of chiropractic treatment on infantile colic in an area where limited evidence exists. Furthermore, the study aims to explore if subgroups of children with suspected musculoskeletal problems will benefit more from the intervention than others. If they obtain better results, this could imply the need for stratified care.

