The study will contribute to establish the effect of chiropractic treatment on infantile colic in an area where limited evidence exists [27]. An increasing number of infants are treated in chiropractic clinics, and the results of the study will be highly relevant for all new parents seeking chiropractic care for their child’s colic. Furthermore, the results will support healthcare professionals in guidance of parents on an evidence based level, which does not exist today. Since associations between infantile colic and both short and long-term consequences for the child and family have been shown [6–8], proper treatment at an early stage might actually present as primary prevention of these disorders. Therefore, a potential positive effect of chiropractic treatment on infantile colic may benefit both individuals and society considerably. Furthermore, serious side effects of chiropractic care in infants have not been reported, and therefore a potential beneficial effect is likely to exceed potential risks [29, 35].

Infantile colic appear to have a multifactorial etiology and it may be unlikely to find one treatment that will fit all [24, 25, 27]. Therefore there is a need to explore if certain subgroups will benefit more from a specific treatment. If confirmed, this could indicate a causal relation and form the basis for a more stratified care that does not exist today.

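### The plan asks whether some subgroups gain more from treatment, but the only method it states is repeating the analyses within strata; no treatment-by-subgroup comparison is stated

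*Protocol article*

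**What the plan says.** All references are to the Protocol article. The Statistical analyses section poses two comparative questions: whether children with suspected musculoskeletal problems gain more than the rest, and whether the effect is larger after a complicated than an uncomplicated birth.

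The stated method for the first is that "all analyses will be repeated stratified for presence of musculoskeletal problems". For the second, "analyses will be repeated stratified for elected factors related to birth". The analyses being repeated are a two-sample t-test on the change in crying hours and a linear regression on baseline crying, randomization group and the stratification factors. That regression has no product term. No section names an interaction test or another comparison of effects between strata.

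The same section calls these analyses exploratory, directs them towards predictors for future studies, and makes them conditional on enough children per stratum.

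Two other places give a subgroup result more weight. The Discussion part of the Abstract says: "If they obtain better results, this could imply the need for stratified care". The main Discussion says: "If confirmed, this could indicate a causal relation and form the basis for a more stratified care". The main Discussion also counts the subgroup analyses among the trial's four main strengths.

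**The concern.** Whether one subgroup gains more than another is a question about the difference between two treatment effects. Two within-stratum estimates, each with its own p-value, do not give that difference or its uncertainty. One stratum can be significant and the other not even when the true effects are identical, because each stratum has only part of the sample.

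This is not a gap that an unseen analysis plan would be expected to fill. The article names a method, and that method does not answer its own question. What is at stake is a stated secondary aim: a chance contrast between strata could be read as support for selecting infants for treatment, or as evidence about the cause of colic.

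**Working it through.** **Inputs (Sample size section).** Difference 1 h: "children in the intervention group will have a reduction of one additional hour, resulting in a reduction of 3.5 crying hours", against 2.5 h in controls. SD: "With an assumption of a common standard deviation of 2.5" hours. Error rates: "a level of significance on 0.05 and a power of 80" per cent. Size: 200 children, 100 per arm. The share of children with musculoskeletal problems or complicated births is not given, so the splits below are assumptions.

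**The plan's own figure.** n per arm = 2 × (1.96 + 0.8416)² × 2.5² / 1² = 98.1, rounded up to 99, or 198 in total. This agrees with 200. A one-sided test would need only 78 per arm, so the design is two-sided. Power at 100 per arm is about 80%.

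**Chance that exactly one of two strata is significant when the true effect is the same in both.** With n per arm in a stratum, SE = 2.5 × √(2/n) and power is about Φ(effect/SE − 1.96), plus a small opposite tail. The chance is p₁(1 − p₂) + p₂(1 − p₁).

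- No effect: 2 × 0.05 × 0.95 = 9.5%.
- 1 h, 50/50 split: SE = 0.50 h, power = Φ(0.04) = 51.6% in each stratum, chance = 2 × 0.516 × 0.484 = 49.9%.
- 1 h, 70/30 split: SEs 0.423 h and 0.645 h, powers 65.8% and 34.1%, chance = 55.0%.

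Simulation of 40,000 trials with t-tests gave 9.5%, 50.0% and 54.9%.

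| Common true effect | 50/50 | 70/30 |
|---|---|---|
| 0 h | 9.5% | 9.5% |
| 0.5 h | 28% | 29% |
| 1.0 h | 50% | 55% |
| 1.5 h | 25% | 37% |
| 2.0 h | 4% | 13% |

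In the hypothesised direction only (musculoskeletal stratum significant, the other not), a common 1 h effect gives 25% at 50/50, and 43% if 70% of children have the problem. If baseline adjustment removed 25% or 50% of the variance (an assumption), the 50% figure would fall to 46% or 31%.

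**Interaction test.** In the simulations its false-positive rate was 5.0% to 5.1% for common effects of 0 h and 1 h at both splits. Its precision, with n₁ and n₂ per arm in the two strata, is SE = 2.5 × √(2/n₁ + 2/n₂), and the difference detectable with 80% power is 2.80 × SE:

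| Split | SE of interaction | Detectable difference |
|---|---|---|
| 50/50 | 0.71 h | 2.0 h |
| 70/30 | 0.77 h | 2.2 h |
| 80/20 | 0.88 h | 2.5 h |
| 90/10 | 1.18 h | 3.3 h |

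At 50/50, power is about 29% for a 1 h difference between strata and 81% for 2 h. About 4 × 198 = 792 children would be needed for 80% power at 1 h. These figures use the unadjusted SD; baseline adjustment would improve them.

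**The case against.** The strongest reply is that the faulty decision rule is inferred. The article says the analyses will be repeated by stratum. It does not say that p-values will be set against each other, and it does not rule out an interaction test. Stratum estimates with standard errors could also be compared directly. The article calls the analyses exploratory, requires sufficient numbers, and phrases its interpretive sentences conditionally. The primary analysis is untouched.

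Much of this stands. The error rates apply only if significance is compared across strata, and the exploratory label limits the consequences. It does not remove the point, because an exploratory analysis still needs to estimate the quantity it asks about, and the article offers no other way of judging the difference.

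A reader might also extend the point to age and chiropractor, since "Analyses will also be performed on the different age and chiropractor strata". The article states no hypothesis of greater benefit for those strata, so the mismatch between question and method does not arise there.

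Finally, the 5% for an interaction test is per test. With four independent interaction tests, the chance of at least one false positive is 1 − 0.95⁴, about 19%.

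**Conclusion.** The point holds for musculoskeletal status and the birth factors: the stated method does not answer the comparative question, and the article attaches possible clinical and causal meaning to the answer. It should be corrected, though it does not affect the primary result.

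A reader might infer that the plan will produce false subgroup differences about half the time. The documents do not support that without conditions. It needs a common true effect close to 1 h, roughly equal strata, unadjusted tests, and a reading that treats significance in one stratum only as a difference. With no treatment effect the figure is about 10%. Across common effects of 0 to 2 h and splits from 50/50 to 90/10 it runs from about 4% to 72%.

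Nor can one detectable difference be fixed in advance. The 2.0 h figure belongs to an assumed 50/50 split and grows as the strata become less equal.

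**What to change.** For musculoskeletal status and each selected birth factor, add the arm-by-subgroup interaction to the planned regression (baseline crying and stratification factors, all children). Report its estimate with a 95% CI as the subgroup result, and show within-stratum effects with CIs as description.

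State that interaction power is low with 200 children: on the unadjusted SD, the detectable difference is about 2.0 h at a 50/50 split, 2.2 h at 70/30 and 2.5 h at 80/20. State also that the 5% error rate is per test.

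Align the sentences on stratified care and a causal relation, in the Abstract and the main Discussion, with the exploratory status that the Statistical analyses section already gives these analyses.

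The cost is some wording and a few model terms, with no new data. The price is less favourable precision for any subgroup claim, because the interval for a difference between strata is wider than that for either stratum alone.
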